#### Quality control

2.8.2

In order to ensure the quality of this trial, we will establish a quality control committee and a data monitoring committee (DMC). DMC comprises 3 independent experts (1 statistician, 1 pulmonologist, and 1 TCM specialist) with no affiliations to the sponsors or research centers. The committee conducts monthly evaluations on the following aspects: protocol adherence (consistency of interventions, compliance with inclusion and exclusion criteria), data accuracy (verification of 10% of CRFs against original documents), and safety profile (analysis of adverse events). Researchers will comply with the guidelines of good clinical practice (GCP). Quality control experts will conduct monthly quality control assessments to ensure the quality of the study. Additionally, all researchers will receive standardized training on the study protocol. Last but not least, enhancing participants’ compliance is another important measure for quality control. Strategies to improve compliance include monthly telephone follow-ups with participants, quarterly home visits for participants, provision of health education materials, and offering appropriate subsidies, etc.

Additionally, an interim analysis will be conducted by the DMC when 50% of follow-up data are accumulated, assessing efficacy, safety, and futility using the O’Brien-Fleming alpha spending function to control type I error. The DMC will recommend continuation, early termination, or modification based on results. Blinding effectiveness will be evaluated post-trial via questionnaires for investigators and participants to guess group allocation. Correct guess proportions will be compared with 50% (random chance) using the chi-square test; non-significant deviation indicates successful blinding.

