### Study design and setting

2.2

This study will conduct a multi-center, randomized, double-blind, placebo-controlled clinical trial. A total of 848 patients with frequent exacerbator phenotype in the stable phase of COPD will participate in this study. After signing the informed consent form, they will be randomly divided into experimental group and control group at a 1:1 ratio. Then, all subjects will receive BFYS granules or placebos for a 52-week intervention period. The flow chart of this trial is demonstrated in Figure 1.

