### Sample size

2.4

The frequency of acute exacerbations is the primary outcome. According to the data in previous studies, the annual frequency of acute exacerbations in the control group was 1.08 episodes (27), and the experimental group is expected to have a 40% reduction (28), i.e., 0.648 episodes. The test level (*α*) and power (1 − *β*) of the hypothesis test were set at 0.05 and 0.9, and the sample size ratio of the experimental group and control group was 1:1. The estimated sample size for each group was 359 participants using PASS software. After accounting for a 15% dropout rate, the required sample size per group was adjusted to 423 participants. Due to the centralized blocked randomization with block sizes of 4, the sample size per group was adjusted to 424 participants. A total of 848 subjects will be enrolled in this trial.

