### Interventions

2.6

Both the experimental group and control group will receive standard treatment as outlined in the “GOLD 2023” (24). Standard treatments permitted in this trial include dual bronchodilators (long-acting muscarinic antagonists [LAMAs] and long-acting beta-2 agonists [LABAs]), triple therapy (inhaled corticosteroids [ICS] combined with LAMA/LABA) for patients with ≥2 moderate exacerbations or ≥1 leading to hospitalization within the past year, and short-acting bronchodilators (e.g., salbutamol) for rescue use. Additionally, the experimental group will be given BFYS granules, while the control group will receive BFYS placebos as an adjunct to standard treatment. The treatment regimen will consist of administering two packages of granules twice daily for 52 weeks. Prohibited treatments include other Chinese herbal preparations with similar formulations or therapeutic effects to BFYS granules, as well as other pharmacological and non-pharmacological treatments that have therapeutic effects on COPD.

BFYS granules and placebos are prepared by Jiangyin Tianjiang Pharmaceutical Co., Ltd. The ingredients of placebos include 5% by weight of the original herbs used in BFYS granules and 95% pure dextrin. This formulation is designed to match BFYS granules in appearance, odor, and taste, which is critical for maintaining double-blinding in TCM trials where sensory differences could unblind participants. Notably, the 5% herbal component is substantially lower than the therapeutic dose of BFYS granules. This proportion is too low to produce meaningful pharmacological effects that could impact the trial’s outcomes. Additionally, the primary and key secondary outcomes are objective, quantifiable metrics, reducing the potential for bias from any minimal, subtherapeutic effects. To ensure the consistency in taste and smell between BFYS granules and the placebo, five professionals not involved in this trial conducted a double-blind sensory evaluation. They scored both using a 1–5 points scale in terms of bitterness, herbal flavor intensity, smell, etc. The results showed that there was no statistical difference in the scores between the two groups (*p* > 0.05), confirming their sensory equivalence. In addition, the appearance, weight, and color of the placebos are the same as those of BFYS granules. All drugs meet national quality standards. The drug components of BFYS granules are shown in Table 1.

**Table 1 tab1:** Components of BFYS granules.

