### Statistical analysis

2.9

SPSS software (Version 25.0) will be used for statistical analysis in this study. The study data will be analyzed according to the ITT principle, where all randomized participants will be included in the analysis according to their original group assignment, regardless of protocol deviations or different follow-up durations. For participants with varying follow-up durations, mixed-effects models for repeated measures will incorporate time as a covariate to utilize available data. Missing data will be handled using mixed-effects models for repeated measures as the primary method, with multiple imputation conducted as a sensitivity analysis. Continuous variables will be expressed as either mean ± standard deviation (assuming normal distribution) or median (interquartile range) (non-normal distribution). For the primary outcome, Poisson regression or negative binomial regression will be used based on overdispersion tests (assuming Poisson or negative binomial distribution). For secondary outcomes: count data will use the same methods as the primary outcome; binary data will use logistic regression (assuming binomial distribution); continuous data will use repeated-measures analysis of variance (for normal distribution) or Friedman test (for non-normal distribution). Mauchly’s test will first be applied to assess sphericity for repeated measures. If the assumption is violated (*p* < 0.05), the Greenhouse–Geisser correction will be implemented. Pairwise comparisons within groups will use the Bonferroni method, between groups the LSD-*t* test (equal variances) or Tamhane’s T2 method (unequal variances). Categorical variables will be presented as frequency (%) and compared using the chi-square test (large samples) or Fisher’s exact test (small samples with <5 expected counts). Outliers will be identified using box plots (values beyond 1.5 × interquartile range), verified for data accuracy, and retained in the primary analysis; sensitivity analyses excluding outliers will be conducted. For all statistical tests, both *p*-values and 95% confidence intervals will be reported. A hierarchical testing strategy will be used for multiple comparisons: the primary outcome will be tested first; if significant, secondary outcomes will be tested with Bonferroni correction to control type I error, aligning with the outcome hierarchy. A *p*-value <0.05 is considered statistically significant.

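### The blinding check reads a non-significant test of end-of-trial guesses against 50% as success, a rule that can give the wrong verdict

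*Protocol article*

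**What the plan says.** Section 2.8.2 (Quality control) gives the timing and the respondents: "Blinding effectiveness will be evaluated post-trial via questionnaires for investigators and participants to guess group allocation". It then gives the test and the reading of it: "Correct guess proportions will be compared with 50% (random chance) using the chi-square test; non-significant deviation indicates successful blinding". The level comes from section 2.9 (Statistical analysis), where a p-"value <0.05 is considered statistically significant".

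Three other places bear on the point. Section 2.2 sets equal allocation ("they will be randomly divided into experimental group and control group at a 1:1 ratio") and 52 weeks of treatment, so guesses are made after a full year of experience with the product. Section 2.4 (Sample size) supplies the expected outcome difference: "the annual frequency of acute exacerbations in the control group was 1.08 episodes", with a 40% reduction to 0.648 under BFYS. Section 2.6 (Interventions) says of the placebo: "This formulation is designed to match BFYS granules in appearance, odor, and taste, which is critical for maintaining double-blinding".

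The text does not say whether guesses are pooled over arms or examined within each arm, nor how many investigators will answer.

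**The concern.** The article commits to a verdict, "non-significant deviation indicates successful blinding", so the issue is a stated decision rule and not a missing detail. Three features are doubtful:

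- A non-significant test is treated as positive evidence. Whether a given departure from 50% is significant depends on the number of respondents, which differs greatly between participants and investigators.
- Guesses made after a year are informed by how the patient fared. If BFYS works, correct guesses rise without any leak of allocation.
- 50% is the chance level for guesses pooled over arms. Within one arm it is the chance level only if half the respondents guess active.

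At stake is how far a positive result will be believed. Exacerbations are defined by symptoms and first captured in patient diaries (section 2.7.1), and CAT and SF-36 are patient-completed (section 2.7.2). A wrong statement about blinding could discredit a sound result or lend false assurance to a doubtful one.

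**Working it through.** **Number of respondents.** From section 2.4: 359 / (1 − 0.15) = 422.4, rounded up to 423, then to 424 as a multiple of 4, and 2 × 424 = 848. The plan's figures reproduce. I use n = 848 (everyone answers) and n = 2 × 359 = 718 (after the planned dropout).

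**The 50% reference.** If a share g guesses active whatever the arm, pooled correct guesses at 1:1 are 0.5g + 0.5(1 − g) = 0.5 for every g. The reference is right for pooled guesses.

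**(a) Dependence on n.** The test becomes significant at 0.5 ± 1.96 × √(0.25/n).
- n = 848: ± 0.0337, so about 53.4% correct is failure.
- n = 718: ± 0.0366, so about 53.7%.
- Investigators: number not given. Assume one independent guess each and a true 65% correct rate. The exact binomial probability of a significant result is 25% with 20 guesses, 36% with 30, 44% with 40 and 66% with 60. Otherwise blinding is declared successful.

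**(b) Perfect blind, effective drug.** Assume a fraction f of participants guess BFYS if they had no exacerbation and placebo otherwise, and that the rest guess independently of allocation. Then pooled correct = 0.5 + f × [P0(0.648) − P0(1.08)] / 2. Here P0(m) = exp(−m) under Poisson, or (1 + km)^(−1/k) under a negative binomial with dispersion k.

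Poisson, f = 1: P0 = 0.523 and 0.340, so pooled correct = 0.5 + 0.1835/2 = 59.2%. Expected chi-square = 4n × 0.0917², about 28.6 at n = 848 and 24.2 at n = 718.

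Probability that blinding is declared failed although it is intact:

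| Model | f | Pooled correct | n = 848 | n = 718 |
|---|---|---|---|---|
| Poisson | 1 | 59.2% | >99% | >99% |
| k = 1 | 1 | 56.3% | 96% | 92% |
| k = 3.22 | 1 | 53.8% | 61% | 53% |
| Poisson | 0.5 | 54.6% | 76% | 69% |
| k = 1 | 0.5 | 53.2% | 45% | 39% |
| k = 3.22 | 0.5 | 51.9% | 20% | 17% |

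The article states no dispersion. The value 3.22 is the one at which the usual negative binomial formula returns 359 per group from the stated rates, alpha and power: (1.96 + 1.2816)² × (1/1.08 + 1/0.648 + 2 × 3.22) / (ln 0.6)² ≈ 359. It serves as a strong-overdispersion case.

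This limb does not need the pooled reading. By arm, with Poisson and f = 1, the control arm is 1 − 0.3396 = 66.04% correct, and chi-square = 4 × 424 × 0.1604² ≈ 43.6, again a failure.

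**(c) Pooled or by arm.** Suppose 80% in both arms guess BFYS, so guesses say nothing about allocation.
- Pooled: (80% + 20%) / 2 = 50%, chi-square 0, p = 1, success.
- By arm, 424 each: 4 × 424 × 0.30² = 152.6 in each arm, failure.
- A milder 60% in both arms: pooled chi-square 0; by arm 4 × 424 × 0.10² = 17.0, p = 0.00004.

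**The case against.** The strongest reply is that this is an ancillary check. It feeds no efficacy analysis, testing hierarchy or stopping rule. The blind is protected by the matched placebo and by the emergency-unblinding procedure, and non-hospitalized exacerbations are also checked against electronic medical records. All of that stands and limits the weight of the point.

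Second, for participants the test is fairly tight: only results within about 3.4 points of 50% pass at n = 848, and section 2.9 promises 95% confidence intervals for all tests. This is partly right. A result just inside the limit has an interval reaching about 53.4% + 3.4% = 56.7% before rounding, which a reader could judge. But the verdict remains tied to the p-value, and the tightness does not carry over to a small group of investigators. If each investigator instead guesses for every patient, there are more guesses, but they are clustered and the simple chi-square no longer applies.

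Third, the probabilities under (b) rest on assumed guessing behaviour and dispersion. That is so, and it is why the result is a range.

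Fourth, a condensed article may leave questionnaire content and the choice between pooled and by-arm analysis to an SAP that is not shown. Those gaps alone would not be a finding. The stated success criterion is.

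A reader might go further and infer that the rule lets real unblinding through because an 80%/20% pattern pools to 50%. The document does not support this. It never says that guesses are pooled. Even if they are, at 1:1 the pooled proportion equals 50% plus half the between-arm difference in guessing active, so exactly 50% means that guesses carry no information on allocation. Passing that pattern is not a missed unblinding; the by-arm reading, which fails it, would be the wrong verdict.

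**Conclusion.** The point holds as a defect in a stated rule: the blinding verdict can be wrong, and its direction depends on respondent numbers, on efficacy and on an unstated choice of analysis.

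That non-significance is no proof of blinding needs no assumption. The 25% to 66% detection range for investigators assumes 20 to 60 independent guesses at a true 65%. The false-failure probability for participants runs from about 20% to above 99% at n = 848 (17% to above 99% at n = 718). It rests on the protocol's rates together with assumed outcome-based guessing and overdispersion. Every case examined is well above the nominal 5%, but the supported statement is that the rule can fail an effective, well-blinded trial, not that it will. The conflict between pooled and by-arm verdicts is exact arithmetic.

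The primary analysis is untouched. What is affected is the credibility statement that accompanies it. Correcting it before analysis is worthwhile and cheap.

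**What to change.** - Delete the sentence that a non-significant deviation indicates success.
- Report guesses by arm, separately for participants and investigators, with Bang's blinding index and its 95% confidence interval. Allow a do-not-know answer and record the reason for the guess.
- State that end-of-trial guesses will be interpreted as possibly reflecting perceived efficacy.

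The cost is wording in the protocol or SAP and two small additions to a questionnaire that is given after the trial. Under Trial status, data collection runs to December 31, 2026 and analysis starts on March 1, 2027.

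Optional: participants not yet past week 13 could also be asked at that existing visit, when guesses are less coloured by outcome. This is only partly feasible, since 582 of 848 were enrolled by August 17, 2025, leaving 266 still to enrol plus those then in their first 13 weeks. Asking early may also prompt participants to think about their allocation. The main correction does not depend on it.

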### Statistical analysis

2.9

SPSS software (Version 25.0) will be used for statistical analysis in this study. The study data will be analyzed according to the ITT principle, where all randomized participants will be included in the analysis according to their original group assignment, regardless of protocol deviations or different follow-up durations. For participants with varying follow-up durations, mixed-effects models for repeated measures will incorporate time as a covariate to utilize available data. Missing data will be handled using mixed-effects models for repeated measures as the primary method, with multiple imputation conducted as a sensitivity analysis. Continuous variables will be expressed as either mean ± standard deviation (assuming normal distribution) or median (interquartile range) (non-normal distribution). For the primary outcome, Poisson regression or negative binomial regression will be used based on overdispersion tests (assuming Poisson or negative binomial distribution). For secondary outcomes: count data will use the same methods as the primary outcome; binary data will use logistic regression (assuming binomial distribution); continuous data will use repeated-measures analysis of variance (for normal distribution) or Friedman test (for non-normal distribution). Mauchly’s test will first be applied to assess sphericity for repeated measures. If the assumption is violated (*p* < 0.05), the Greenhouse–Geisser correction will be implemented. Pairwise comparisons within groups will use the Bonferroni method, between groups the LSD-*t* test (equal variances) or Tamhane’s T2 method (unequal variances). Categorical variables will be presented as frequency (%) and compared using the chi-square test (large samples) or Fisher’s exact test (small samples with <5 expected counts). Outliers will be identified using box plots (values beyond 1.5 × interquartile range), verified for data accuracy, and retained in the primary analysis; sensitivity analyses excluding outliers will be conducted. For all statistical tests, both *p*-values and 95% confidence intervals will be reported. A hierarchical testing strategy will be used for multiple comparisons: the primary outcome will be tested first; if significant, secondary outcomes will be tested with Bonferroni correction to control type I error, aligning with the outcome hierarchy. A *p*-value <0.05 is considered statistically significant.

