#### Withdrawal/termination criteria

2.3.4

Patients with any of the following conditions will be withdrawn or terminated from the intervention, but will continue to be followed for outcome assessment and included in the Intention-To-Treat (ITT) analysis according to their original group assignment, unless truly lost to follow-up:

(1) Patients who experience serious adverse reactions or allergies after taking BFYS granules. In this study, serious adverse reactions include events that result in death, are life-threatening, require hospitalization or prolongation of existing hospitalization, or lead to persistent or significant disability/incapacity.(2) Patients who have disease progression, such as uncontrolled AECOPD or concurrent severe illnesses (e.g., acute cardiovascular events).(3) Patients who commit serious protocol violations, including unauthorized use of prohibited medications, or ≥4 consecutive weeks of non-adherence to study drugs.(4) Patients who show poor treatment response, with worsened symptoms or a ≥ 10% decline in FEV1 compared to baseline at any 13-week assessment visit.(5) Patients who enroll in other clinical studies.(6) Patients who voluntarily request to withdraw from the intervention.

Complete loss to follow-up refers to patients with objective inability to follow up due to severe physical impairment, geographical relocation, or confirmed cognitive decline, resulting in the inability to conduct any outcome assessments. These patients will be withdrawn from the study, and their data will be handled according to the ITT principle with missing data addressed using mixed-effects models for repeated measures and multiple imputation in sensitivity analyses.

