#### Primary outcome

2.7.1

The primary outcome is the frequency of AECOPD after the interventions. AECOPD is defined as an acute exacerbation process characterized by dyspnea and/or increased coughing and expectoration (11). The frequency will be recorded every 13 weeks, and the total number over the 52-week treatment period will be calculated. A lower number in a specified period indicates better efficacy.

To ensure complete documentation, participants will record daily respiratory symptoms in the specialized subject diary. For AECOPD-related symptoms, details including onset time and specific symptoms must be documented. Diaries will be submitted weekly and reviewed by researchers every week. Non-hospitalized exacerbations will be verified at the 13-week follow-up using the diary, patient reports, and electronic medical records. For hospitalizations at study sites, the team will retrieve medical records within 48 h using the patient-signed authorization. For hospitalizations at external facilities, patients must notify the team within 72 h and provide complete hospitalization records. The total number of exacerbations will be summarized, confirmed, and entered into the Case Report Form (CRF) at each 13-week visit.

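### The primary AECOPD count model names no exposure term, and the one stated provision for unequal follow-up belongs to a different model that does not supply one

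*Protocol article*

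**What the plan says.** Section 2.7.1 (Primary outcome) defines the variable as a total: "The frequency will be recorded every 13 weeks, and the total number over the 52-week treatment period will be calculated". It adds the direction: "A lower number in a specified period indicates better efficacy".

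Section 2.9 (Statistical analysis) names the model: "For the primary outcome, Poisson regression or negative binomial regression will be used based on overdispersion tests". No offset, exposure or person-time term is mentioned. The same section puts every randomised participant in the analysis, "regardless of protocol deviations or different follow-up durations".

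For unequal follow-up, section 2.9 says: "For participants with varying follow-up durations, mixed-effects models for repeated measures will incorporate time as a covariate to utilize available data". For missing data it says: "Missing data will be handled using mixed-effects models for repeated measures as the primary method, with multiple imputation conducted as a sensitivity analysis". Section 2.3.4 (Withdrawal/termination criteria) gives the same two methods for complete loss to follow-up. It also keeps patients who stop treatment under observation, "unless truly lost to follow-up".

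Death is a secondary outcome in section 2.7.2. No rule says how a death, or a partly observed year, enters the exacerbation count.

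**The concern.** These statements do not fit together. The outcome is a count accumulated over time, so a patient observed for half a year has half the opportunity to have an event. In a Poisson or negative binomial model, an offset of log observed time handles this. The article instead points to a repeated-measures mixed model with time as a covariate. In its usual meaning that is a model for repeated continuous measurements, and time in it describes a trajectory, not the length of the risk period. A single 52-week total per patient also has no repeated measures for it to use.

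The primary rate ratio is at stake. With lower counts counted as better, missing exposure lowers an arm's apparent rate. Any difference between arms in observed time then passes into the treatment estimate, in either direction.

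**Working it through.** **Inputs from the article.** Section 2.4 gives a control rate of 1.08 per year, a 40% reduction, α 0.05, power 0.90, 359 per group before dropout and 15% dropout. The final size is 424 per group.

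**The plan's own figures.** The experimental rate is 1.08 × 0.60 = 0.648. Dropout inflation is 359 / 0.85 = 422.4, rounded up to 423, then 424 for blocks of 4, and 848 in total. These reproduce. The 359 does not follow from the stated inputs alone. With two-sided α,

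n = (1.960 + 1.282)² × (1/1.08 + 1/0.648 + 2k) / (ln 0.60)²,

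which gives about 100 per group for Poisson (k = 0) and 180 for k = 1. It reaches 359 at a dispersion of k ≈ 3.22, which the article does not state. I use this only to choose a range for k (0, 1 and 3.22). It is not part of the present point.

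**Assumptions.** Loss times are uniform over the year, so a lost patient contributes 0.5 year on average. Loss is unrelated to exacerbation risk. The article gives 15% loss overall; the splits between arms are mine, chosen so that they average 15%.

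**Bias without an exposure term.** Mean follow-up in an arm with loss d is 1 − 0.5d. At the control rate, a half-year patient is expected to contribute 1.08 × 0.5 = 0.54 events. The expected rate ratio without an offset is

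true ratio × (1 − 0.5 d_BFYS) / (1 − 0.5 d_placebo).

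| Loss BFYS/placebo | Mean follow-up (years) | Factor | True 1.00 becomes | True 0.60 becomes |
|---|---|---|---|---|
| 15%/15% | 0.925/0.925 | 1.000 | 1.00 | 0.60 |
| 20%/10% | 0.900/0.950 | 0.947 | 0.95 | 0.57 |
| 25%/5% | 0.875/0.975 | 0.897 | 0.90 | 0.54 |
| 5%/25% | 0.975/0.875 | 1.114 | 1.11 | 0.67 |

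**Type I error.** Simulation used 424 per group, gamma-Poisson counts, 4,000 runs, and a two-sided Wald test of the log rate ratio with empirical variance:

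| Loss BFYS/placebo | No offset, k = 0 | k = 1 | k = 3.22 |
|---|---|---|---|
| 15%/15% | 0.054 | 0.047 | 0.047 |
| 20%/10% | 0.114 | 0.098 | 0.066 |
| 25%/5% | 0.335 | 0.199 | 0.107 |

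With an offset, type I error lay between 0.041 and 0.059 in every cell, and the estimates returned to about 1.00 and 0.60. A repeat with another random seed agreed to within about 0.01.

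**Loss of power in the reverse case.** At 5%/25% with a true ratio of 0.60 and k about 3.2, power is about 93% with an offset and 77–79% without.

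**Interim.** Section 2.8.2 places it at 50% of follow-up data. Assume this means person-time, with even recruitment over the 18 months in the Trial status section. Half of 848 person-years (424) is reached at 1.25 years, because (848/1.5) × (0.25 + 0.5) = 424. By then (848/1.5) × 1.25 ≈ 707 patients are enrolled, and (848/1.5) × 0.25 ≈ 141 have a full year. About 80% have a partial year, but staggered entry is balanced by randomisation. A null simulation of this look without an offset (1,000 runs, k = 1 and 3.2) gave mean ratios of 1.00 and 1.01 and about 6% rejection, so no bias appears.

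**The case against.** The strongest reply is that the offset is unstated, not excluded. Section 2.4 reasons in annual frequencies, and an offset is the kind of model detail often left to an analysis plan, which is not shown here. That is correct as far as it goes, and a reader should not conclude that the sponsor has decided against an offset. But the article is not silent on unequal follow-up. It states a method, and that method is not the model named for the primary outcome. Nor is the mixed model confined to the continuous secondary outcomes: section 2.9 assigns those to repeated-measures analysis of variance or the Friedman test.

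A second reply is that counts are recorded every 13 weeks, so a mixed count model on the four intervals may be intended. This is possible, but the text does not say so, and a partly observed interval would still need an exposure term.

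A third is that a patient lost early without an event does not enter as a full-year zero, because the article treats unobserved follow-up as missing. This stands. The full-year zero is something a reader might infer from combining a total with an all-randomised analysis; the document does not state it. The figures above therefore hold only if totals are analysed without an exposure term.

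Fourth, continued observation after treatment stops limits the loss, and equal loss leaves the ratio unbiased. Both stand.

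**Conclusion.** The point holds as a badly fixed method for the primary analysis: a count model with no named exposure term, paired with a follow-up provision that belongs to another model. If totals are analysed without exposure, the rate ratio is off by the ratio of mean follow-up: nothing at equal loss, about 5% at a 20%/10% split and about 10% at 25%/5%. Type I error is then about 7–11% and 11–34% respectively for dispersion from 0 to 3.2. This rests on uniform, non-informative loss times and on assumed splits of the planned 15%.

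Three stronger readings are not supported:

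- **That the gap favours BFYS.** It does so only if BFYS loses more follow-up or loses it earlier. The reverse split turns 0.60 into about 0.67.
- **That the interim look is more biased.** Partial years there come mainly from staggered entry, which is balanced between arms. What is lacking is a defined analysis and some precision.
- **That choosing Poisson or negative binomial by an overdispersion test is an error of similar weight.** It is a stated rule with no quantified harm. Naming negative binomial directly is simply cleaner.

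**What to change.** In section 2.9, state the primary model as negative binomial regression with a log link and offset log(time observed). Time at risk runs from randomisation to the earliest of death, loss to follow-up or week 52. Report the rate ratio with its 95% confidence interval. Use the same offset for hospitalised AECOPD and at the interim.

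Limit the mixed model for repeated measures, in sections 2.9 and 2.3.4, to the continuous repeated outcomes. An offset assumes non-informative loss, and section 2.3.4 lists severe physical impairment among the reasons for complete loss. So keep multiple imputation of the unobserved count as a sensitivity analysis, and say how deaths are treated in it.

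The cost is a few sentences. The planned 848 does not change. The one practical requirement is a last-contact date for each patient. The article does not list this as a collected item, but the weekly diaries and 13-week visits in section 2.7.1 should supply it. Analysis is scheduled to begin on March 1, 2027, so the change can be made beforehand; it should also precede the interim look.
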